### Sample size and power analysis

The proposed study is a two-arm cluster randomized controlled trial with the church as the unit of randomization. Thus, there are two important sample size estimates: N, the number of pregnant women; and K, the number of churches, with the pregnant women nested within the K churches. We reviewed the total annual infant baptisms in churches located in Enugu and Oji-River for 2010 to estimate the potential number of pregnant women. Our review indicated that there were 20,700 infant baptisms conducted in 2010. Further analysis showed that in 2010, Enugu and Oji-River each contained about 50 churches that had 200 infant baptisms and 40 churches that had at least 100 infant baptisms (Table 
1).

**Table 1 T1:** Infant baptisms in churches

**Enugu Local Government Area**	**Oji-River Local Government Area**
Catholic Churches: 9,300 infant baptisms	Catholic Churches: 9,000 infant baptisms
Anglican Churches: 1,400 infant baptisms	Anglican Churches: 1,000 infant baptisms

Power calculations were performed using the module ‘Inequality Tests for Two Proportions in a Cluster-Randomized Design’ in PASS 11, which implements methods of Donner and Klar
[46]. That module approximates power for simple two-sample binomial tests for data collected in clusters with non-zero intra-cluster correlation (ICC). The Proc GLIMMIX analysis should have superior power since inclusion of covariates should reduce variability. For all three hypotheses, there will be 40 clusters (churches). For all three, there is an anticipated Control Group rate between 15% and 25%
[1,8]. The usual recommendation is to take ICC between 0.002 and 0.05; ICC as high as 0.10 is considered quite high. The PASS module chooses a cluster size (number of individuals per cluster), which determines the total sample size as cluster size X, no. of clusters. Table 
2 shows minimum detectable Intervention Group rates for various cluster sizes, Control Group rates, and ICC. The total sample size is driven by Secondary Hypothesis 2, where the CG rate should be around 0.20, and the intervention is expected to more than double the rate. From the preceding Table 
2, it appears safe to target between cluster sizes 3 and 4, for a total sample size of 140 HIV-infected women. Using the average of 6% of pregnant women infected with HIV, and a possible 10% dropout rate (from our experience during scale up of community HIV testing), that would require (140/0.06)/0.9 or approximately 2,700 total pregnant women (1,350 per group). Clearly, any interesting increase in rate for the intervention group is detectable for such a large total sample size for Hypotheses 1 and 2 (Table 
2).

**Table 2 T2:** Minimum detectable intervention group rate (2-sided test, 5% significance level)

**Cluster size (total sample size)**	**Control group rate**								
	**0.15**			**0.20**			**0.25**		
	**ICC**			**ICC**			**ICC**		
	0.002	0.05	0.1	0.002	0.05	0.1	0.002	0.05	0.1
3 (120)	0.37	0.38	0.39	0.43	0.44	0.45	0.49	0.50	0.51
4 (160)	0.34	0.35	0.36	0.40	0.41	0.43	0.46	0.47	0.49
5 (200)	0.31	0.33	0.35	0.38	0.39	0.41	0.43	0.45	0.47
10 (400)	0.26	0.29	0.31	0.32	0.35	0.37	0.38	0.41	0.43
50 (2000)	0.20	0.24	0.27	0.25	0.30	0.33	0.31	0.36	0.39

Number of churches needed (K): We need to have 1,350 pregnant women in each arm of the study and follow them through pregnancy and up to six weeks post-delivery. Since pregnant women will be recruited at different stages of pregnancy, we will need to end recruitment five months after the study is open to recruitment and allow time to follow the last recruited pregnant women through nine months of pregnancy and up to six to eight weeks post-delivery (approximately eleven months). According to our review of infant baptisms in churches in our proposed study area, there were more than 50 churches with 200 infant baptisms per year (an average of 16 per month) and 20 churches with more than 100 infant baptisms per year (an average of 8 per month). We will need to recruit 15 of the large churches and 5 of the small churches in each arm to reach our sample size of 1,350 pregnant women in each arm over a 5-month period. Table 
1 illustrates the flexibility we have with respect to both recruitment and attrition. For example, if our recruitment goal is an average of 16 pregnant women per month in a church with 200 infant baptisms per year, but it turns out we were only able to recruit an average of 12 participants per month, it means we will need to add and randomize 5 more churches (15 + 5 = 20) to maintain our level of statistical power. Note however, that our proposed primary analysis plan below is intent to treat (ITT), so we will analyze all participants who are randomized and who have completed initial testing even if they drop out later. Thus the above power analysis is conservative.

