## Background

Globally, Sub-Saharan Africa (SSA) accounts for 76% of all women living with HIV and an estimated 90% of the 3.4 million children living with HIV. A total of 22 priority countries have been identified by the WHO that account for 90% of pregnant women living with HIV. Nigeria is one of only 4 countries among the 22 with an HIV testing rate for pregnant women of less than 20%
[1,2]. Studies have shown that when HIV-infected women are treated with antiretroviral therapy and their infants receive antiretroviral (ARV) prophylaxis, mother-to-child transmission of HIV (MTCT) occurs in less than 1% of pregnancies
[3-6]. Despite the availability of simple, less expensive and highly effective ARV regimens capable of being implemented in resource-limited settings, 75,000 Nigerian infants were infected in 2010
[1,7]. During that year, only 14% of pregnant women were tested for HIV, while 9% of pregnant women living with HIV received WHO recommended antiretroviral (ARV) therapy, and only 11% of HIV-exposed infants received ARV prophylaxis for prevention of mother-to-child HIV transmission (PMTCT) resulting in an estimated 75,000 HIV-infected infants in 2010
[1,8]. Currently, most pregnant women must access a healthcare facility (HF) to be screened and receive available PMTCT interventions. This clinic-based approach is challenging when only 35% of pregnant women deliver in an HF and only 2.9% of HFs have an established PMTCT program
[8,9]. Finding new approaches to translate evidence-based interventions in PMTCT to sustainable community-based programs is necessary to realize the WHO/PEPFAR goal of eliminating new pediatric infections by 2015
[10].

Various reasons have been identified as barriers to HIV testing and PMTCT completion. Low perception of personal risk, poor access to testing sites, cost, confidentiality, and HIV-related stigma have all been identified as barriers to HIV testing
[11-14]. Barriers to optimal PMTCT exist at the level of the patients and providers, but barriers at the health systems level appear to have more adverse impact on healthcare in general
[15-17]. Most women in Nigeria do not access prenatal care early in pregnancy, and only 35% of pregnant women deliver in a health facility where just 2.9% have an established PMTCT program

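### The sample-size step from 140 HIV-infected women to 2,700 enrolees omits the chance that an infection is identified; at the plan's own control testing rate only about 11–18 control women would be identified, not 70

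*Protocol article*

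**What the plan says.** All of this is in the protocol article, mainly under Sample size and power analysis.

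- The driver of N: "The total sample size is driven by Secondary Hypothesis 2, where the CG rate should be around 0.20". Secondary Hypothesis 2 is PMTCT completion among HIV-infected women. On the size of effect, the section adds that "the intervention is expected to more than double the rate".
- The target, read from Table 2 between 3 and 4 infected women per church over 40 churches: "for a total sample size of 140 HIV-infected women".
- The conversion to enrolment: "that would require (140/0.06)/0.9 or approximately 2,700 total pregnant women (1,350 per group").
- The control assumption: "For all three, there is an anticipated Control Group rate between 15% and 25" per cent. Hypothesis 1 is HIV testing of pregnant women, so this range covers testing too. The Background gives a national figure for 2010: "only 14% of pregnant women were tested for HIV".
- Table 2 is headed "Minimum detectable intervention group rate (2-sided test, 5% significance level"). It does not state its power.

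Description of the control condition/usual care says that control churches do not offer the on-site laboratory tests. Under Outcome measures, control testing is confirmed at the facility where the woman reported prenatal care. The sample-size section closes by limiting the analysis to participants who completed initial testing and by calling the power calculation conservative.

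**The concern.** A woman can enter the PMTCT comparison only if her infection is known. The conversion from 140 to 2,700 allows for prevalence and dropout but not for identification, so it treats every infected woman as identified in both arms. For the control arm this conflicts with the same section's expectation that 15–25% of control women are tested.

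The hypothesis that sets the size of the whole trial would then have well under the power that Table 2 suggests. A non-significant PMTCT result could be read as absence of effect when the comparison had little chance of detecting the planned doubling.

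**Working it through.** **Inputs.** From the article: two-sided 5% level; 20 churches per arm; control completion about 0.20; intervention completion more than double that (0.42 used here); ICC 0.05 (middle of the tabulated values); 1,350 women per arm; prevalence 6%; dropout 10%; control testing 15–25%. Inferred: 80% power for Table 2. Assumed, because the article gives no figure: 80% of infected intervention women identified (varied to 100%).

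**1. Reproduce Table 2.** Let n be women per arm, m = n/20, DE = 1 + (m − 1) × ICC, and e = n/DE. Then

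power = Φ[(|p₂ − p₁| − 1.96 s₀)/s₁], with s₁² = p₁(1 − p₁)/e₁ + p₂(1 − p₂)/e₂.

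In the unpooled test s₀ = s₁. In the pooled test s₀² = p̄(1 − p̄)(1/e₁ + 1/e₂). At 80% power all 45 cells reproduce within 0.006 unpooled and 0.011 pooled. At 90% power they are off by up to 0.04–0.05. Hence the inferred 80%.

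**2. Reproduce N.** 3.5 × 40 = 140, and 140/0.06/0.9 = 2,593, which the article rounds up to about 2,700. The division is correct; what is missing is a factor.

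**3. Add identification.** Infected and retained per arm: 1,350 × 0.06 × 0.9 = 72.9. Identified in the control arm:

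- 72.9 × 0.15 = 10.9
- 72.9 × 0.20 = 14.6
- 72.9 × 0.25 = 18.2

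That is 0.5–0.9 per church, against the 3–4 used to read Table 2. Identified in the intervention arm at 80%: 72.9 × 0.80 = 58.3.

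**4. Power for 0.20 against 0.42, ICC 0.05.**

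As planned, 70 against 70: DE = 1 + 2.5 × 0.05 = 1.125 and e = 62.2. With p̄ = 0.31, s₀ = 0.0829 and s₁ = 0.0805, so Φ[(0.22 − 0.1625)/0.0805] = 0.76 pooled. Unpooled gives 0.78.

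With 14.6 against 58.3: control DE is set to 1 because there is less than one woman per church. Intervention DE = 1.096 and e = 53.2. With p̄ = 0.373, s₀ = 0.143 and s₁ = 0.125, so Φ[(0.22 − 0.280)/0.125] = 0.32 pooled.

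| Control testing | Identified, control / intervention | Power, pooled | Power, exact Fisher, no clustering | Detectable rate at 80% power, pooled |
|---|---|---|---|---|
| 15% | 10.9 / 58.3 | 24% | 23.6% (11 v 58) | 0.64 |
| 20% | 14.6 / 58.3 | 32% | 29.5% (15 v 58) | 0.59 |
| 25% | 18.2 / 58.3 | 38% | 31.5% (18 v 58) | 0.56 |
| As planned | 70 / 70 | 76% | 77% | 0.43 |

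**5. Vary the assumptions.**

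- All infected intervention women identified (72.9): pooled power is 25%, 32% and 39% at 15%, 20% and 25% control testing.
- Control testing 50% (36.5 identified), intervention 80–100%: power is 58–61% pooled and 63–67% unpooled.
- No dropout: 1,350 × 0.06 = 81 infected per arm, of whom 12–20 are identified in the control arm.
- Control enrolment needed to identify 70 women: 70/0.06/0.9/0.25 = 5,185 up to 70/0.06/0.9/0.15 = 8,642, against 1,350 planned.

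**The case against.** **Control identification may exceed 15–25%.** Previous HIV testing is listed as a covariate, so some control women may already know they are infected, and priests and study staff encourage facility care. This stands: a reader might infer that only women tested in this pregnancy can count, and the article does not say so. The 11–18 is therefore conditional. But the article gives no figure for either effect, and at 50% control testing power still falls short of 80%.

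**A control-arm test may be described elsewhere.** Figures 1 and 2 are not shown and this is a condensed article, so that cannot be excluded. The text on the control condition and on outcomes points the other way.

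**The denominator could be all infected women, tested or not.** Untested women have unknown status. Moreover, 20% completion among all infected women with 15–25% tested would require 0.20/0.25 = 80% to 0.20/0.15 = 133% of tested women to complete.

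**Trial status expects 5,400 participants.** This may include male partners. If all were women, the control count would double to about 22–36, still about half of 70 or less.

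**Replacement figures are fragile with so few control women.** This stands. A reader carrying Table 2's unpooled formula over to 15 against 58 would get 42% power and a detectable rate of 0.55. Exact Fisher power for 0.20 against 0.55 at 15 against 58 is only 69%, before any clustering. Agreement with Table 2 at equal arms does not validate that formula here. Nor is 58 a plan figure: it follows from the assumed 80%.

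**Conclusion.** The point holds as an omitted assumption in the calculation that sets N. At the plan's own 15–25% control testing rate, with no study test described for control women, about 11–18 infected control women would be identified instead of 70. For 0.20 against 0.42, power drops from about 76–78% to about 24–38% (pooled), or about 24–32% by exact Fisher without clustering. The detectable rate rises from about 0.43 to about 0.56–0.64. These figures rest on an ICC of 0.05, on Table 2's inferred 80% power, and on 80% identification in the intervention arm; raising that last value to 100% changes little.

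A reader might infer that the trial as a whole is underpowered. The article does not support that. HIV testing is measured in all enrolled women, and 2,700/40 = 67.5 per church exceeds Table 2's largest row (50 per church), where a control rate of 0.20 already gives detectable rates of 0.25–0.33. The shortfall concerns Secondary Hypothesis 2 only, so this should be fixed but does not put the primary result at risk.

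**What to change.** In Sample size and power analysis:

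1. Add an identification probability, by arm, to the step from 140 to 2,700, and state the assumed values and their source, including any allowance for previously known status.
2. Restate for Secondary Hypothesis 2 the expected identified women per arm, the power and the detectable rate. Use a small-sample method that suits unequal arms, and tabulate over control testing rates of 15–50% and stated intervention testing rates. State the power that Table 2 uses.
3. For this hypothesis, withdraw the statements that the target of 3–4 per church is safe and that the power analysis is conservative.

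Enrolment and conduct stay as they are. The cost is a recalculation and a less favourable stated detectable effect for one secondary hypothesis.

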### Statistical methods

All three hypotheses test for differences in two binomial proportions at follow-up. Clustering effects must be incorporated in the analysis since data collected on parishioners within the same church could be expected to exhibit correlation, while data collected on parishioners in different churches should exhibit minimal correlation. Generalized linear mixed models as implemented in PROC GLIMMIX in SAS 9.3
[47] provide a rich set of tools for analyzing such data. Data will be analyzed with that procedure using a logit link function and the binomial distribution. These are multilevel models allowing incorporation of covariates and confounders for the individual (such as age, household income, education level, previous HIV testing, last menstrual period, marital status, employment status, male’s partners’ previous HIV test results, and situational/contextual factors) and cluster-level (*i.e.*, church) covariates and confounders such as size of church and congregation type (Anglican or Catholic). For all three hypotheses, a preliminary (and similar) analysis will model the probability that an individual declines participation; any significant predictors from that model will be used in the main analysis to reduce confounding. Statistical significance will be set as p-value <0.05 and tests will be 2-sided.

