### Church recruitment

One of the most common barriers to recruitment of churches to participate in clinical trials involves the suspicion with which faith-based organization views the scientific community. We had anticipated that this might impact our recruitment, but to our surprise, we had such a willingness and insistence to participate from the priests that the 200 churches in the four dioceses all wanted to participate in the study. They saw the program as an evangelical tool to encourage and increase the number of males who traditionally do not attend church services regularly. Pregnant women in churches that were not initially selected were reportedly going to close by churches that were participating in the program. To avoid the potential impact of unstructured participation, we used a spoke-and-hub approach to include all the churches. Each initially selected church acts as a coordinating hub for surrounding churches that follows the randomization group of their coordinating church. This provided an organized method of expanding the number of churches to accommodate the high uptake without disrupting the randomization and follow-up schedule in the study. Baby shower receptions were held at the coordinating churches, while recruitment occurs at each individual church.

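### After the hub-and-spoke expansion the randomised unit is the hub group (40), but the analysis section still names the church as the cluster and does not redefine it

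*Protocol article*

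**What the plan says.** All references are to the protocol article.

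- **Design.** Sample size and power analysis describes a "two-arm cluster randomized controlled trial with the church as the unit of randomization" and counts 40 clusters for all three hypotheses. Trial status also speaks of 40 churches.
- **Analysis.** Statistical methods equates the cluster level with the church, lists church size and denomination as cluster-level covariates, and supports the model by the expectation that "data collected on parishioners in different churches should exhibit minimal correlation". It specifies a logit mixed model in PROC GLIMMIX. The test level is fixed there: "Statistical significance will be set as p-value <0.05 and tests will be 2-sided".
- **What happened.** Church recruitment, under Challenges and limitations in the Discussion, reports that "the 200 churches in the four dioceses all wanted to participate in the study" and that "we used a spoke-and-hub approach to include all the churches". On allocation it says: "Each initially selected church acts as a coordinating hub for surrounding churches that follows the randomization group of their coordinating church". On delivery: "Baby shower receptions were held at the coordinating churches, while recruitment occurs at each individual church".

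The Discussion presents this as a redesign already in operation and says that it left the randomisation intact. It mentions no matching change to the analysis.

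**The concern.** A cluster trial is analysed by the unit that was randomised. The attached churches were not randomised; they inherited an arm. There are therefore still 40 independent allocations, each now covering about five congregations.

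Churches under one hub are also unlikely to be uncorrelated. In the intervention arm the test is offered at the baby shower, and one hub's shower serves several churches. In the control arm women are referred to the nearest facility, which neighbouring churches may well share.

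The independence argument in Statistical methods fits 40 separate churches. It does not fit churches that share a hub. An analyst who follows that section literally, with data recorded at each recruiting church, could put the random intercept on about 200 congregations. The standard error of the arm effect would then leave out the correlation between churches of one hub. The p-value and confidence interval for the primary outcome are the main things at stake.

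**Working it through.** **Inputs from the article.** 40 randomised churches; about 200 churches after the expansion; 2,700 women; 140 HIV-infected women for PMTCT completion; ICC 0.002, 0.05 and 0.10; control rate 0.15 to 0.25; two-sided 5%.

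**Assumptions.** The article gives neither the number of churches per hub nor the correlation between churches of one hub. I take 200/40 = 5 equal churches per hub, all enrolling, so 2,700/40 = 67.5 women per hub and 2,700/200 = 13.5 per church. Let ρc be the ICC within a church and ρh the correlation between women in different churches of the same hub. I let ρh be 0, ¼, ½ or all of ρc.

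**Step 1: reproduce Table 2.** I used a two-proportion z-test with design effect 1 + (m − 1) × ICC and 20 clusters per arm. At 80% power with unpooled variance, all 45 cells come out within 0.006. Example, m = 50, control rate 0.20, ICC 0.05: the design effect is 1 + 49 × 0.05 = 3.45, and the detectable rate is 0.30, as tabulated. The planned power thus rests on 40 clusters.

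**Step 2: type I error if the model is fitted by individual church.**

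- Modelled design effect = 1 + 12.5 × ρc
- Actual design effect = 1 + 12.5 × ρc + 54 × ρh, where 54 = 67.5 − 13.5
- Type I error = 2 × {1 − Φ(1.96 × √(modelled/actual))}

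| ρc | Modelled | Actual at ρh = ¼, ½, 1 × ρc | Type I error at ¼, ½, 1 |
|---|---|---|---|
| 0.002 | 1.025 | 1.052, 1.079, 1.133 | 5.3%, 5.6%, 6.2% |
| 0.05 | 1.625 | 2.300, 2.975, 4.325 | 9.9%, 14.7%, 23% |
| 0.10 | 2.250 | 3.600, 4.950, 7.650 | 12.1%, 18.6%, 28.8% |

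At ρh = 0 the two design effects are equal and the error is 5%. Example, ρc = ρh = 0.05: √(1.625/4.325) = 0.613, 1.96 × 0.613 = 1.20, and the two-sided tail is 0.23.

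**Step 3: check by simulation.** 20,000 runs per case with 40 hubs, 5 churches per hub, 13 women per church and a control rate of 0.20, comparing t-tests on church means with t-tests on hub means. With ρh at ¼, ½ and all of ρc, church-level rejection was 5.3%, 5.7% and 6.4% at ICC 0.002; 9.9%, 14.8% and 22.6% at 0.05; and 12.5%, 18.6% and 29.1% at 0.10. Hub-level rejection was 4.6% to 5.2% in every case.

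**Step 4: PMTCT completion.** 140/40 = 3.5 women per hub and 140/200 = 0.7 per church, so a church effect can absorb almost none of the clustering. The modelled design effect is about 1; the actual one is 1 + 2.5 × ICC = 1.005, 1.125 and 1.25. Type I error is 5.1%, 6.5% and 8.0%.

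**Step 5: what hub-level analysis does to power.** With 40 hubs of 67.5 women, control rate 0.20 and 80% power, the minimum detectable rate is 0.248, 0.297 and 0.332 at ICC 0.002, 0.05 and 0.10. Table 2 gives 0.25, 0.30 and 0.33 for cluster size 50.

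**The case against.** A reader might infer that the trial will be analysed as about 200 independent clusters, so that its standard errors are too small for all three hypotheses. The article does not support that.

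- **No such count appears.** The only number of clusters given is 40. The article ties every added church to its coordinating church, so a model with 40 hub clusters is at least as compatible with the text.
- **The quoted sentence is a rationale, not a model statement.** No random-effect term or degrees-of-freedom method is given, and an article may leave those to an analysis plan that is not shown.
- **Inflation is conditional.** It needs fitting by individual church and also a positive correlation between churches of one hub, which the article does not quantify. The 23% and 29% figures are the extreme in which women in different churches of a hub are as alike as women in one church. At ICC 0.002 the rise is about one percentage point at most.
- **The shared-shower argument is weaker in the control arm**, where no on-site test is offered. Nor does the article say that attached churches share the hub's study team.

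All of this stands, and it limits the point. It does not remove it. The section does more than leave detail out: it states an independence expectation between churches that the article's own account of the expansion undercuts, and nothing tells the analyst what a church now is. The shortfall rule in the sample size section speaks of adding and randomising further churches, so it gives no guidance for churches added without randomisation.

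**Conclusion.** The point holds as an unrevised definition of the cluster, not as a demonstrated anti-conservative analysis. Only 40 hub groups were randomised, and the analysis section should say that they are the clusters.

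If the model were fitted by individual church, the primary test could run anywhere from its nominal 5% to about 29% over the article's own ICC range, depending on a correlation that is not known. The exposure is much smaller for PMTCT completion. Partner testing was not calculated separately.

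The figures rest on equal hub and church sizes, all 200 churches enrolling, the article's ICC range applied at both levels, and tests of cluster means standing in for the logit mixed model.

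**What to change.** Revise Statistical methods to state that:

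1. the cluster, and the random-effect unit in every model, is the hub church with its attached churches (40 groups);
2. church may be added as a second random effect nested within hub;
3. arm is tested on degrees of freedom based on the 40 hubs (40 − 2 = 38, less any hub-level covariates);
4. low correlation is expected between hub groups, not between churches of the same hub.

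Record a hub code and a church code for each participant. Trial status reports 2,000 of 5,400 participants recruited, so the codes may have to be added for those already enrolled.

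The cost is a short change of wording and the two codes. Intervals may be wider than under a church-level fit, but the detectable rate for the primary outcome stays close to Table 2's row for cluster size 50, so the planned power is essentially kept.
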